### Developing a Sampling Frame

#### Overview

The study used a 2-stage, random sampling approach. In the first stage, random locations (ie, places where female sex workers solicit clients or engage in sex and where men who have sex with men cruise or engage in sex) were selected from a previously validated list. In the second stage, participants were randomly selected from the locations on a randomly selected day of the week.

#### Stage 1 Sampling

As a first step, the ePBS study team developed the sampling frame by validating lists of mapped locations in Nairobi County where female sex workers and men who have sex with men solicit clients, cruise, meet sexual partners, and engage in sexual activities. The sample frame was derived from a programmatic mapping exercise conducted in 2018 [6]. The lists were updated—that is, closed locations were removed and newly emerged locations were added—through a validation process facilitated by the study team members who are in regular, direct contact with key population members. Through this validation process, population size estimates for each location, the days and times when these locations are operational, and the days when the locations have the highest number of female sex workers or men who have sex with men were verified and revised, as needed, via a standardized approach.

The lists of validated locations (1 each for female sex workers and men who have sex with men) formed the sampling frames representing the universe of locations across Nairobi County. Key population members spending time within a given location tend to be more homogeneous, in terms of typology and risk behavior, than those in different locations [27]. As such, potential participants for each PBS session were randomly selected from a single location. During the first stage of sampling, 99 locations (equal to the number of PBS sessions planned for each group) were randomly selected such that 1 PBS session was conducted per selected location. The random selection of key population group–specific locations from which potential participants were identified was stratified by subcounty and location typology.

#### Stage 2 Sampling

In stage 2 of sampling, each of the 99 randomly selected locations was randomly allocated to an assigned week and day on which potential participants were enrolled from the location. For example, data collection for this ePBS study was projected to take 30 days; for each location, 1 week (ie, from weeks 1 to 4 of the study period) was randomly selected first, followed by the random selection of 1 specific day within that chosen week. This process determined the precise week and day that each selected location was designated for the study. Ultimately, 10 to 12 potential participants were randomly approached by community researchers at the location on the specified day and week and invited to take part in the study.

This 2-stage sampling approach ensured that participants were representative of the total population of the key population group by geography (subcounty) and location typology across days of the week, yielding a comprehensive and diverse sample of participants from communities of female sex workers and men who have sex with men in Nairobi County.

### Study Procedure

The overall flow of the ePBS study procedure from participant identification and enrollment to PBS, BBS, and FGD (every fifth PBS session) is outlined in Figure 1. The duration to complete PBS and BBS was 120 minutes, including 10 minutes for initial screening and consent, 60 minutes for the PBS, 20 minutes for pretest counseling, and 30 minutes for BBS. For every fifth PBS group participating in an FGD, an additional 45 to 60 minutes was added to their total estimated participation time.

**Figure 1 figure1:**
[figure not shown]
Expanded PBS study procedure flowchart used to collect data from female sex workers and men who have sex with men in Nairobi, Kenya, from April to May 2023. BBS: behavioral and biological survey; FGD: focus group discussion; PBS: polling booth survey; PrEP: pre-exposure prophylaxis; SWOP: Sex Workers Outreach Program.

### Participant Enrollment and Data Collection Site Preparation

Potential participant enrollment occurred at selected locations on the allocated days of the week, according to the study’s sampling frame. Enrollment primarily occurred in the late afternoon or evening on the day of data collection to increase the likelihood of meeting a higher number of female sex workers or men who have sex with men in the location. Peer educators and outreach workers from the SWOP clinics facilitated the identification of potential participants within their own key population group. They were responsible for introducing potential participants to the study and assessing their eligibility. Any eligible individuals were provided with detailed information about ePBS. If eligible participants were interested in participating in the study, they were brought to the data collection site by peer educators and outreach workers. As much as possible, data collection occurred within the selected locations. Ahead of participant enrollment, the study team members scouted selected sites to identify suitable spaces for safe and confidential data collection. Team members were responsible for setting up stations for PBS and private, quiet locations for face-to-face structured interviews and biological sample collection. If the selected sites posed challenges (eg, logistical or safety challenges) for data collection, prescouted alternate locations nearby were used instead.

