**Methods:**

The novel ePBS approach employs complementary data collection methods, expanding upon the traditional polling booth survey (PBS) method by incorporating additional quantitative, qualitative, and biological data collection components and an improved sampling methodology. Quantitative methods will include (1) PBS, a group interview method in which individuals provide responses through a ballot box in an unlinked and anonymous way, and (2) a behavioral and biological survey (BBS), including a face-to-face individual interview and collection of linked biological samples. Qualitative methods will include focus group discussions. The ePBS study uses a 2-stage, population- and location-based random sampling approach involving the random selection of locations from which random participants are selected at a predetermined time on a randomly selected day. PBS data will be analyzed at the group level, and BBS data will be analyzed at an individual level. Qualitative data will be analyzed thematically.

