### Target Sample Size Calculation

To be representative of each key population group, the study’s sampling strategy was based on probability sampling techniques that provided an equal chance to all members of the study populations, meeting defined inclusion criteria, to be included in the study. The determination of an appropriate sample size for a single study domain is usually based on the following considerations: (1) the number of measurement units in the population, (2) the parameter of interest, and (3) the degree of confidence by which the parameter is estimated and the desired level of precision.

One objective of our study was to estimate the HIV prevalence and incidence among female sex workers and men who have sex with men in Nairobi County. As such, sampling parameters were set with the prevalence and sample size having 95% statistical confidence, with a desired precision of +5% or –5%.

The sample size for PBS and BBS study was calculated using the following formula: *n* = [1.96^2^*p*(1 – *p*)(*DEFF*)]/*d*^2^. Where *p* is HIV prevalence, *DEFF* is the design effect of the sampling approach, and *d* is the desired precision.

The finite population correction factor is then applied to the derived sample size using the following formula: *nf* = (*n **
*N*)/[(*n* + (*n* – 1)]. Where *nf* is the sample size adjusted for finite population correction, *n* is the sample size required, and *N* is the population size.

To calculate the sample size for this ePBS study, we used the most recent estimate of HIV prevalence among female sex workers (26%) and men who have sex with men (12%) in Nairobi, as reported in a 2017 study conducted by NASCOP [7]. The sample size calculation was adjusted to accommodate an anticipated nonresponse rate of 15%. The final target sample size, adjusted for population size and nonresponse, for female sex workers was n=769 and for men who have sex with men was n=420. Ideally, each PBS session comprises 10 to 12 participants; the total target sample sizes for female sex workers and men who have sex with men were divided by 12 to determine the total number of PBS sessions required for each key population group, that is, 64 PBS sessions with female sex workers and 35 sessions with men who have sex with men.

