## Results

The study enrolled 759 female sex workers (response rate: 759/769, 98.6%) and 398 men who have sex with men (response rate: 398/420, 94.7%) across 64 and 35 PBS sessions, respectively (Table 2).

In total, 758 (99.9%) female sex workers (1 participant refused participation in BBS) and 398 (100%) men who have sex with men participated in the face-to-face interview for the BBS, and all (n=1156) provided blood and urine samples for rapid tests. In total, 14.79% (171/1156) of participants (female sex workers: n=101, 59.1%; men who have sex with men: n=70, 40.9%) tested positive for HIV via rapid test. Among those testing positive, 93.6% (160/171) of participants (female sex workers: n=100, 62.5%; men who have sex with men: n=60, 37.5%) provided consent for venous blood sample collection. Three whole blood samples from female sex worker participants were discarded due to missing bar codes on the sample tubes. A total of 73 participants reported currently receiving PrEP in the BBS face-to-face interview (Table 2), and rapid urine tests were conducted on the samples from these participants (female sex workers: n=56, 77%; men who have sex with men: n=17, 23%).

**Table 2 table2:** Expanded polling booth survey (ePBS) participant enrollment and data collection among female sex workers and men who have sex with men in Nairobi County, Kenya, from April to May 2023 (n=1157).

	Female sex workers (n=759), n (%)	Men who have sex with men (n=398), n (%)
PBS participants	759 (100)	398 (100)
BBS^a^ participants	758 (99.9)	398 (100)
HIV rapid tests conducted	758 (99.9)	398 (100)
Reactive HIV rapid test results	101 (13.3)	70 (17.6)
Venous blood samples collected	100 (13.2)	60 (15.1)
Urine tests conducted	56 (7.4)	17 (4.3)

^a^BBS: behavioral and biological survey.

A total of 20 FGDs were completed with female sex workers (n=14, 70%) and men who have sex with men (n=6, 30%).

Data cleaning and analysis are ongoing. Aggregate responses from each PBS session and individual data from BBS respondents have been entered into separate data modules in the data entry software. The data will then be exported to SPSS (version 28.0; IBM Corp) for analysis. Weights will be applied to data during analyses to account for the sampling design and to adjust for unequal selection probabilities. CIs will be calculated, and descriptive analyses of the PBS and BBS data will be performed separately to address the study objectives.

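### The hour of enrolment was not drawn at random, so the claim that all members had an equal chance of selection does not hold; estimates cover people present at the enrolment hours

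*Protocol article*

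**What the plan says.** **What was randomised.** Under Stage 2 Sampling, each of the 99 selected locations gets a random week, "followed by the random selection of 1 specific day within that chosen week". No draw of a time slot is described. The abstract matches this: "random participants are selected at a predetermined time on a randomly selected day".

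**How the hour was chosen.** Under Participant Enrollment and Data Collection Site Preparation: "Enrollment primarily occurred in the late afternoon or evening on the day of data collection to increase the likelihood of meeting a higher number". The stated reason is yield.

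**What the frame holds.** Stage 1 Sampling says that the validation of the location lists covered "the days and times when these locations are operational".

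**What is claimed.** Target Sample Size Calculation speaks of "probability sampling techniques that provided an equal chance to all members of the study populations", for those who meet the inclusion criteria. Stage 2 Sampling says that participants represent the whole key population "by geography (subcounty) and location typology across days of the week". Time of day is not in that list.

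**What is planned in analysis.** Results: "Weights will be applied to data during analyses to account for the sampling design and to adjust for unequal selection probabilities". The article names no component for hour of enrolment or frequency of attendance. The Limitations section does not mention coverage by hour.

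**The concern.** In venue-based sampling, a person's chance of selection depends on whether the venue is drawn and on whether the person is there when the team enrols. Randomising the day spreads the second part across the week. Choosing the hour for yield tilts it towards people who attend at busy times.

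If people who attend at other hours differ in HIV status, in experience of violence or in contact with the programme, the estimates describe the late-afternoon and evening population and not all female sex workers or men who have sex with men in the county. HIV prevalence, violence and contact coverage are all named outcomes, and coverage is to be compared with targets. The Objectives also present the method as a pilot for scaling up, so an unqualified equal-chance claim would carry over to later rounds.

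**Working it through.** **1. The passages side by side.** Write a person's selection probability as P(location drawn) × P(person present at the enrolment day and hour) × P(person approached, given presence). The article randomises location, week and day, and says that those present are approached at random. It does not randomise the hour. For two people at the same location on the same days, one there every evening and one there only in the morning, the middle term differs. Equal chance for all members would need it to be equal for everyone, and a yield-chosen hour does not make it so. For someone never present when the team enrolled, the term is zero.

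**2. What weights can do.** A design weight is 1/probability.
- *Probability zero:* the weight is undefined and the person cannot be recovered.
- *Probability small but known:* weighting works, at a cost in variance. Assume that 10% of the population is off-hours.
  - At one tenth of the evening chance, their sample share is 0.10×0.1/(0.10×0.1 + 0.90) = 0.01/0.91 = 1.1%. That is about 8 of 758 female sex workers and 4 of 398 men, each with relative weight 10. The Kish design effect is (0.011×10² + 0.989)/(0.011×10 + 0.989)² = 1.73.
  - At one half of the evening chance, the share is 0.05/0.95 = 5.3%, about 40 and 21 people, and the design effect is only about 1.04.
- Such weights need the enrolment hour and usual attendance. The article does not say that either was recorded.

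**3. Possible size, zero-chance case only.** The plan gives no figure to reproduce here. Full-population prevalence minus covered prevalence is s × (p_out − p_in), where s is the share with zero chance. For p_in, take the reactive rapid tests in Table 2: 101/758 = 13.3% and 70/398 = 17.6%, unweighted. The documents give neither s nor p_out. Assume s of 5%, 10% or 30%, and p_out between half and twice p_in. For example, with s = 10% and p_out = 2 × p_in among female sex workers: 0.10 × (26.6 − 13.3) = 1.3 points.

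| s (assumed) | Female sex workers, points | Men who have sex with men, points |
|---|---|---|
| 5% | −0.3 to +0.7 | −0.4 to +0.9 |
| 10% | −0.7 to +1.3 | −0.9 to +1.8 |
| 30% | −2.0 to +4.0 | −2.6 to +5.3 |

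A positive value means that the survey estimate is too low.

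**4. Set against sampling error.** The design effect is not stated. A value of 2.25 reproduces the targets closely, with the standard finite population correction and division by 0.85 for nonresponse: 770 against 769, and 420 against 420. With it, the half-width is 1.96 × √(2.25 × 0.133 × 0.867/758) = 3.6 points for female sex workers and 1.96 × √(2.25 × 0.176 × 0.824/398) = 5.6 points for men. At 5–10% excluded, the shift is well below sampling error. At 30% it can exceed the half-width for female sex workers and come close to it for men. A confidence interval would not reveal it in either case.

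**The case against.** The case for the authors is substantial.

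- **It is partly disclosed.** The abstract says openly that the time was predetermined, and the representativeness sentence names subcounty, typology and day of week, not hour.
- **The text says primarily.** Some enrolment may have taken place at other hours, so a reader who infers that no weight could help goes too far. Only people never present at any enrolment hour are beyond weighting, and nothing shows how many there are.
- **The same hours for every type of venue is an inference.** The enrolment section does not mention typology. Times set location by location from the verified operating hours would fit the text, and the full protocol may give the rule. No closing hour is given for evening, so exclusion of late-night workers is not shown either.
- **Busy hours are sensible fieldwork.** Each session needs 10 to 12 people from one location on one visit, for about 120 minutes, or 45 to 60 minutes more with a focus group, and under safety constraints. A random quiet hour risks an unfilled session.

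A reader might also infer that contact coverage is overstated because outreach keeps the same hours as enrolment. Outreach hours are never stated, so that direction is conjecture.

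All of this limits the strength of the point. None of it rescues the equal-chance sentence, which is a positive statement about the design that the article's own account of enrolment contradicts. Disclosure in the abstract does not make the chances equal, and an unseen weighting scheme cannot give weight to people who could not be sampled.

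**Conclusion.** The point holds as a matter of the stated population. Week and day were random and no random draw of the hour is described. The hour was chosen mainly for yield. The equal-chance claim is therefore wrong as written, and the claim to represent the whole key population needs a limit on time of day that the article does not give.

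The existence, size and direction of any bias are unknown from the documents. The prevalence ranges above rest on assumed excluded shares and prevalence ratios, and on zero inclusion; they are too wide for people who are only mainly active at other hours and can still be sampled. They show that the effect could be negligible or could matter, and no single figure should be quoted. The documents do not support calling the sample unusable, or calling random start hours a required change. The correction is minor, but it alters what the estimates can be said to describe.

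**What to change.** 1. **Restate the population.** Under Target Sample Size Calculation, replace the equal-chance statement. Under Stage 2 Sampling, qualify the claim to represent the whole key population. In both, say that estimates refer to eligible people present at listed locations during the enrolment hours, mainly late afternoon or evening.
2. **Add a limitation.** State that the hour was not sampled, that people active only at other hours may be missed, and that the planned weights do not correct for those with no chance of selection.
3. **If session times were recorded,** show HIV prevalence, contact coverage and violence by session-time band as a sensitivity analysis, separately for each population. Sessions outside the main hours may be few, time band may be mixed up with typology, and the comparison says nothing direct about people never present.
4. **Use the verified operating times** to describe which listed locations, by typology, operate mainly outside the enrolment window. These times describe locations, not headcounts by hour, so this is a description and not an estimate of undercoverage.

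Items 1 and 2 need no data. Items 3 and 4 need a short table if the records exist. The downside is a narrower population claim.

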### Ethical Considerations

#### Informed Consent

At the data collection site, before ePBS data collection commenced, prevention officers, with the support of community researchers, guided participants through the informed consent process, ensuring that all participants understood and were comfortable with the information included in the consent form. Any questions from potential participants were addressed before commencing the study. Nonconsenting or unwilling participants were thanked for their time and excluded from the study. All eligible participants who provided written or verbal informed consent received a unique identifying code that was used for the BBS portion of the study.

#### Participant Compensation

Participants received compensation for their time and travel at a standard local rate of Ksh 500 (US $5). Those participating in FGDs received an additional Ksh 500 (US $5) for their extra time.

#### Safety

Conducting research studies with key populations who are criminalized in Kenya requires careful consideration to ensure community safety. Before initiating data collection, extensive consultations with key population communities were conducted. The primary objectives of the study and the methodology were shared and explained during these consultations. Feedback obtained from the community was instrumental in shaping the study procedures to ensure the communities’ safety and comfort. Furthermore, a collaborative partnership with Nairobi County authorities was established to enhance the safety and protection of both the study teams and the key populations and participants. The study teams carried official identity cards and study approval letters to show that they were conducting an official study. The data collection took place in locations where female sex workers and men who have sex with men generally congregate and that were considered to be safe. Location managers were sensitized and informed about the study ahead of implementation. Study team members were trained in crisis management and were provided a protocol to follow in case of an emergency or a breach in safety for the study team or participants. A team of supervisors, including senior team members of PHDA and Nairobi County officials, visited the sites each day for supervision and support.

#### Ethics Approvals

The research study has received ethics approvals from Amref Health Africa Ethics and Scientific Review Committee, Kenya (Amref ESRC P1365/2022); Health Research Ethics Board, University of Manitoba, Canada (HS25883); National Commission for Science, Technology, and Innovation, Kenya (NACOSTI/P/23/24009); and Nairobi City County, County Health Research Ethics Committee (NCCG/HWN/REC/349).

#### Privacy and Confidentiality

All investigators have completed a web-based course on the protection of human participants in research and have obtained certificates. Furthermore, investigators and all study team members have signed data confidentiality agreements with PHDA, pledging to uphold the highest standards of data privacy and security.

During the informed consent process, female sex workers and men who have sex with men participating in the study were clearly informed of their right to withdraw from the study at any point if they so desired. This withdrawal did not affect their access to the services provided by SWOP clinics. The potential benefits and risks associated with participating in the study were thoroughly explained to the participants during the informed consent process.

